| Duration of treatment per participant:  | Screening period: 14 to 42 days prior to Baseline                                                                                                                                                                                                                                                                                                                                                                                                                                                                                                                                                                                                                                                                                                                                                                                                                                                               |
|                                                | Primary Treatment period: 12 weeks                                                                                                                                                                                                                                                                                                                                                                                                                                                                                                                                                                                                                                                                                                                                                                                                                                                                              |
|                                                | Continued Treatment period: To Week (W) 24                                                                                                                                                                                                                                                                                                                                                                                                                                                                                                                                                                                                                                                                                                                                                                                                                                                                      |
| Study procedures:                       | 
Subjects will provide voluntary written informed consent and be screened for eligibility. Eligible subjects will return at Baseline (Day [D] 0) to be randomised to receive their first treatment.
 
Subjects will be required to remain in the clinic for twenty four hours after the administration of IMP at W0 and 4. Two further treatments will be given, one each at W8 and 12. Subjects will remain in the clinic for a minimum of 8 hours after administration of IMP.
 
Subjects will be followed up through clinic visits at each of the assessment visits at the end of D3 and W2, 6, 10, 13, 14, 16 and 24.
 
Adverse events (AEs), clinical laboratory parameters (haematology, chemistry) and concurrent medications will be recorded throughout the study.
 
Immunogenicity will primarily be assessed at W14 with plasma and PBMC stored at selected clinic visits.
 |
| Contraindications to further dosing:    | Treatment related Grade 3 or 4 toxicity.                                                                                                                                                                                                                                                                                                                                                                                                                                                                                                                                                                                                                                                                                                                                                                                                                                                                        |
| Safety parameters:                      | Refer to Table 1                                                                                                                                                                                                                                                                                                                                                                                                                                                                                                                                                                                                                                                                                                                                                                                                                                                                                                |
| Clinical procedures / assessments:      | Refer to Table 1                                                                                                                                                                                                                                                                                                                                                                                                                                                                                                                                                                                                                                                                                                                                                                                                                                                                                                |
| Specialised analyses:                   | 
T-cell immunogenicity will be primarily assessed by interferon gamma Enzyme-Linked Immunosorbent Spot assay (ELISpot) at Baseline and W13 and 14 (1 and 2 weeks after the last vaccination). Peptides assessed will be pools of 15mers overlapping by 11 amino acids and spanning C clade Gag Durban Consensus sequence.
 
Other exploratory immunological assays may be performed (such as viral suppression and intracellular cytokine staining).
                                                                                                                                                                                                                                                                                                                                                                                                                                                 |
| Sample size determination:              | This is a first in human phase I study with the primary objective of assessing safety. As such, no formal statistical hypothesis will be tested. Twenty seven subjects will be included in the study, including 18 active and 9 placebo. A total of 18 subjects receiving active treatment will give at least reasonable power to detect severe treatment related toxicities at rates of 20% or greater.                                                                                                                                                                                                                                                                                                                                                                                                                                                                                                        |
| Statistical analyses:                   | 
This is a first-in-man phase I study and, as such, no formal statistical hypothesis will be tested.
 
Safety will be examined through AEs, vital signs and routine laboratory screening (haematology and clinical chemistry).
 
Immunogenicity will be assessed through T-cell immunogenicity.
                                                                                                                                                                                                                                                                                                                                                                                                                                                                                                                                                                                                 |
| Committees / guidelines:                | A Data Safety Monitoring Board (DSMB) will provide independent review of the safety data in this study.                                                                                                                                                                                                                                                                                                                                                                                                                                                                                                                                                                                                                                                                                                                                                                                                         |
| Special protocol requirements / issues: | None                                                                                                                                                                                                                                                                                                                                                                                                                                                                                                                                                                                                                                                                                                                                                                                                                                                                                                            |

Table 1: Table of Assessments

| Assessment                                                               | Screening    | Baseline       |      |           | On-Study Period |     |          |      |           |     |          |      |           |     |           |      |           |     |     |     | Exit |
|--------------------------------------------------------------------------|--------------|----------------|------|-----------|-----------------|-----|----------|------|-----------|-----|----------|------|-----------|-----|-----------|------|-----------|-----|-----|-----|------|
|                                                                          | D-42 to D-14 | D0 to D1* Dose |      |           | D3              | W2  | W4* Dose |      |           | W6  | W8* Dose |      |           | W10 | W12* Dose |      |           | W13 | W14 | W16 | W24  |
|                                                                          |              | Pre            | Post | Discharge |                 |     | Pre      | Post | Discharge |     | Pre      | Post | Discharge |     | Pre       | Post | Discharge |     |     |     |      |
| Informed Consent                                                         | X            |                |      |           |                 |     |          |      |           |     |          |      |           |     |           |      |           |     |     |     |      |
| Medical History                                                          | X            |                |      |           |                 |     |          |      |           |     |          |      |           |     |           |      |           |     |     |     |      |
| Eligibility determination                                                | X            | X              |      |           |                 |     |          |      |           |     |          |      |           |     |           |      |           |     |     |     |      |
| Randomisation                                                            |              | X              |      |           |                 |     |          |      |           |     |          |      |           |     |           |      |           |     |     |     |      |
| Full Physical Examination                                                | X            | (X)            | (X)  | (X)       | (X)             | (X) | (X)      | (X)  | (X)       | (X) | (X)      | (X)  | (X)       | (X) | (X)       | (X)  | (X)       | (X) | (X) | (X) | X    |
| Targeted Physical Examination                                            |              | X              | X    | X         | X               | X   | X        | X    | X         | X   | X        | X    | X         | X   | X         | X    | X         | X   | X   | X   |      |
| Demography, Height                                                       | X            |                |      |           |                 |     |          |      |           |     |          |      |           |     |           |      |           |     |     |     |      |
| Body weight                                                              | X            | X              |      |           | X               | X   | X        |      |           | X   | X        |      |           | X   | X         |      |           | X   | X   | X   | X    |
| Vital Signs                                                              | X            | X              | X    | X         | X               | X   | X        | X    | X         | X   | X        | X    | X         | X   | X         | X    | X         | X   | X   | X   | X    |
| Electrocardiogram**                                                      | X            | X              | X    |           |                 |     | X        | X    |           |     | X        | X    |           |     | X         | X    |           |     |     |     |      |
| Urine β-HCG pregnancy test                                               | X            | X              |      |           |                 |     | X        |      |           |     | X        |      |           |     | X         |      |           |     |     | X   | X    |
| Urine drug screen                                                        | X            | X              |      |           |                 |     | X        |      |           |     | X        |      |           |     | X         |      |           |     |     |     |      |
| HIV # /Hepatitis C virus/Hepatitis B surface antigen serology | X            |                |      |           |                 |     |          |      |           |     |          |      |           |     |           |      |           |     |     |     |      |
| Haematology and biochemistry                                             | X            | X              | X    | X         |                 | X   | X        | X    | X         | X   | X        | X    |           | X   | X         | X    |           | X   | X   | X   | X    |
| Adverse event review                                                     |              | X              | X    | X         | X               | X   | X        | X    | X         | X   | X        | X    | X         | X   | X         | X    | X         | X   | X   | X   | X    |
| Concurrent Medications review                                            | X            | X              | X    | X         | X               | X   | X        | X    | X         | X   | X        | X    | X         | X   | X         | X    | X         | X   | X   | X   | X    |
| Admission to the clinic                                                  |              | X              |      |           |                 |     | X        |      |           |     | X        |      |           |     | X         |      |           |     |     |     |      |
| 24 hour stay                                                             |              | X              |      |           |                 |     | X        |      |           |     |          |      |           |     |           |      |           |     |     |     |      |
| 8 hour stay                                                              |              |                |      |           |                 |     |          |      |           |     | X        |      |           |     | X         |      |           |     |     |     |      |
| Administration of investigational medicinal product                      |              | X              |      |           |                 |     | X        |      |           |     | X        |      |           |     | X         |      |           |     |     |     |      |
| HIV viral load and CD4+ T-cell count                                     | X            | X              |      |           |                 |     | X        |      |           |     | X        |      |           |     | X         |      |           |     |     | X   | X    |
| Immunogenicity testing                                                   |              | X              |      |           |                 |     |          |      |           |     |          |      |           | X   | X         |      |           | X   | X   | X   |      |
| Response to clade C peptides                                             | X            |                |      |           |                 |     |          |      |           |     |          |      |           |     |           |      |           |     |     |     |      |
| Human Leukocyte Antigen typing                                           |              | X              |      |           |                 |     |          |      |           |     |          |      |           |     |           |      |           |     |     |     |      |

(X) As clinically indicated

\* Visit conducted via telephone on D5, 7, 31, 59 and 87 for adverse event review and concurrent medications

\*\* Including continuous cardiac monitoring on treatment days

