**Table 4: Grading Scale where AIDS Clinical Trial Group Toxicity Grades Do Not Apply**

| Grade   | Severity         | Definition                                                        |
|---------|------------------|-------------------------------------------------------------------|
| Grade 1 | Mild             | Aware of sign or symptom, but easily tolerated                    |
| Grade 2 | Moderate         | Discomfort enough to cause interference with usual activities     |
| Grade 3 | Severe           | Incapacitating with inability to work or perform usual activities |
| Grade 4 | Life-threatening | Participant is at immediate risk of death                         |

The relationship to study product therapy should be assessed using the following definitions:

- Unrelated:** AE is clearly due to extraneous causes (e.g. underlying disease, environment)
- Unlikely:** The temporal association between the AE and IMP is such that IMP is not likely to have any reasonable association with the AE
- Possible:** The AE could have been produced by the subject's clinical state or IMP
- Probable:** The AE follows a reasonable temporal sequence from the time of IMP administration, abates upon discontinuation of the IMP and cannot be reasonably explained by the known characteristics of the subjects clinical state
- Definite:** The AE follows a reasonable temporal sequence from the time of IMP administration, abates upon discontinuation of the IMP and/or reappears when IMP is re-introduced

These criteria in addition to good clinical judgment should be used as a guide for determining the causal assessment. If it is felt that the event is not related to IMP, then an alternative explanation should be provided.

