## **9.6 Guidance for toxicity management**

AEs and abnormal laboratory values will be graded according to the Toxicity Grading Scale (Appendix A). IMP will be interrupted or discontinued due to toxicity according to the toxicity grading scale.

All abnormal values should be confirmed by repeat testing within 3 calendar days of receipt of results prior to dose adjustment or interruption, unless such a delay is not consistent with good medical practice. For the purpose of monitoring toxicities, the baseline value is defined as the last value prior to the administration of the first dose of study medication. The value must be obtained from the central laboratory. All assessments of toxicity will be based on changes from this value, regardless of later interruptions to dose.

The following table (Table 5) outlines the procedure for temporary or permanent IMP discontinuation due to an AE or SAE. All subjects who experience a study product related AE should be followed until resolution of the AE, even if the subject has interrupted or discontinued study product.

Table 5: Toxicity management.

| Clinical or laboratory* abnormality                                | Action Taken                                     |                                                                                           |
|--------------------------------------------------------------------|--------------------------------------------------|-------------------------------------------------------------------------------------------|
|                                                                    | Continue dosing at Investigator discretion       | Permanently discontinue dosing                                                            |
| Grade 1                                                            | Regardless of causality                          | N/A                                                                                       |
| Grade 2                                                            | Regardless of causality                          | N/A                                                                                       |
| Grade 3
Lab events of clinical significance*
Clinical Events | Unrelated to treatment
Unrelated to treatment | Unknown or at least possibly related
Unknown or at least possibly related # |

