| Grade 4
Lab events of clinical significance*
Clinical Events | Unrelated to treatment
Unrelated to treatment | Unknown or at least possibly related
Unknown or at least possibly related              |

\* All grade 3 or 4 laboratory abnormalities must be confirmed by repeat testing as soon as possible, preferably within 24 hours of receipt of results prior to dose interruption or discontinuation, unless such a delay is not consistent with good medical practice.

#The Investigator may continue dosing at their discretion for transient and self limiting events that may be attributed to IMP but are expected for a vaccine (such as fever): these grade 3 event(s) must be followed to resolution ( $\leq$  grade 2) before the subject is discharged from the clinic.

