### **11.3 Withdrawal of subjects from Study Product**

Section 9.6 provides guidance for dose modification or discontinuation of IMP in the event of AEs or abnormal laboratory values.

If a subject permanently discontinues dosing with IMP (for example, as a result of an AE), every attempt should be made to keep the subject in the study and continue to perform the required follow-up and procedures. The ideal is to continue to follow the subject for the full study period or until resolution of the AE. If it is not possible for the subject to remain in the study for the full study period, every attempt should be made to keep the subject in the study up to W16. If the subject remains in the study but off study treatment, all study procedures should continue as per protocol or equivalent assessments during the on-study period, such as pre-dosing study assessments at W4, 8 and 12.

If the subject will not remain in the study for all study related procedures, the Exit Evaluation should be performed wherever possible.

All subjects who discontinue IMP dosing should be followed for at least 30 days after the last dose of IMP in order to monitor subjects for possible post-treatment AEs which may occur after IMP has been discontinued.

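### For related grade 3 clinical events that are transient and expected for a vaccine, the synopsis bars further dosing while the Table 5 footnote permits it

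*Protocol*

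**What the plan says.** - **Synopsis, contraindications to further dosing:** the whole entry is "Treatment related Grade 3 or 4 toxicity". It carries no qualifier.
- **Section 9.6, Table 5:** grade 3 and grade 4 events, both clinical events and laboratory events of clinical significance, fall under "Permanently discontinue dosing" when their relation to treatment is "Unknown or at least possibly related". Dosing may continue when they are unrelated. Only the grade 3 clinical entry carries the # marker.
- **Table 5, # footnote:** "The Investigator may continue dosing at their discretion for transient and self limiting events that may be attributed to IMP but are expected", the expectation being tied to vaccines, with fever as the example. A condition follows: "these grade 3 event(s) must be followed to resolution", meaning grade 2 or lower, before the subject leaves the clinic.
- **Section 11.3:** "Section 9.6 provides guidance for dose modification or discontinuation of IMP in the event of AEs or abnormal laboratory values".
- **Section 9.2.1, causality scale:** five levels, namely Unrelated, Unlikely, Possible, Probable and Definite. Unlikely is defined by timing: "The temporal association between the AE and IMP is such that IMP is not likely" to have a reasonable association with the event.

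**The concern.** This is the stopping rule for the individual subject in a first-in-human study whose primary objective is safety. If two current passages disagree, two staff members following the protocol in good faith could treat the same event differently. One would withhold the remaining doses and the other could give them.

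What is at stake is the exposure of a subject who has already had a related grade 3 event, and the chance to observe recurrence on re-dosing. Escalation rests on safety data from two immunisations and one week of follow-up (Section 4.1), and the DSMB reviews each cohort after the Week 4 dose (Section 10). Whether a subject with such an event after dose 1 receives dose 2 therefore affects the data on which escalation is decided. Investigators are blinded (Section 7.2), so the rule is applied to placebo recipients as well as to active subjects.

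**Working it through.** The protocol has no figure on this point to reproduce. The check is a comparison of current passages.

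**Step 1. Events judged related to treatment**

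| Event | Synopsis | Table 5 with # footnote | Agree? |
|---|---|---|---|
| Grade 3 clinical; transient, self-limiting, expected for a vaccine | Further dosing contraindicated | Continuation allowed at the Investigator's discretion, with follow-up to grade 2 or lower before discharge | No |
| Grade 3 clinical, any other | Contraindicated | Permanent stop | Yes |
| Grade 3 laboratory, of clinical significance | Contraindicated | Permanent stop | Yes |
| Grade 4 clinical, or laboratory of clinical significance | Contraindicated | Permanent stop | Yes |

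The conflict is confined to the first row. Fever, the footnote's own example, shows it: Appendix A grades 39.4 to 40.5°C as grade 3. If a fever in that range is judged related and settles before discharge, the synopsis rules out the next dose and the footnote allows it.

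**Step 2. Doses affected**

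Four doses are planned, at Day 0 and Weeks 4, 8 and 12 (Section 4.2). If the event follows dose k, the doses still open are 4 − k:

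- after dose 1: 4 − 1 = 3
- after dose 2: 4 − 2 = 2
- after dose 3: 4 − 3 = 1
- after dose 4: 4 − 4 = 0, so the conflict has no dosing effect

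**Step 3. Causality labels for grade 3 and 4 events**

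| Section 9.2.1 level | Table 5 column label |
|---|---|
| Unrelated | Continue |
| Unlikely | Matches neither label |
| Possible, Probable, Definite | Stop |
| (not on the scale) | Unknown: stop |

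The synopsis differs slightly here too: it speaks only of treatment-related toxicity, whereas Table 5 also stops dosing when the relation is unknown.

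**Step 4. Does the Section 12.2 safety signal depend on this?**

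The signal is three or more of the 18 active subjects with a related toxicity of at least grade 3. With n = 18, the exact binomial P(X ≥ 3) at true rates of 5%, 10%, 20% and 30% is 5.8%, 26.6%, 72.9% and 94.0%, as stated in the protocol. The count is by subject. A subject with one such event is already counted, so giving or withholding later doses does not change that subject's status.

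**The case against.** The best defence is that Table 5 is plainly the operative text. Section 9.6 presents it as the procedure for stopping study product, and Section 11.3 sends the reader there. The trial-halting rule in Section 10 carries a parallel note on expected, self-limiting vaccine reactions. The synopsis entry is a one-line summary with no procedure behind it. The footnote is also permissive: it never requires a dose that the synopsis bars. Much of this stands, and it makes the synopsis look like a summary that lags the body. But no clause gives Section 9.6 precedence, and an entry headed as a contraindication is not one that site staff should be expected to disregard.

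Four stronger readings are tempting, and the protocol does not support them:

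- **That the footnote opens dosing after any related grade 3 event.** It does not. It is limited to clinical events that are transient, self-limiting and expected for a vaccine, and it carries a resolution condition.
- **That a number of affected subjects can be stated.** The rates in Section 12.2 concern all severe related toxicity. Nothing gives a rate for this narrower class.
- **That the prespecified safety signal is distorted.** It counts subjects, as Step 4 shows. What remains is individual exposure and the chance of recurrence, which cannot be quantified from the protocol.
- **That an Unlikely event leaves the Investigator with no guidance at all.** The scale is ordered, and Unlikely lies below a threshold of at least possible relation, so it does not trigger the stop column by that wording. The continue column nevertheless names only unrelated events, and Unknown remains undefined. This is a labelling gap, secondary to the main point.

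**Conclusion.** The inconsistency is real and narrow. For related grade 3 clinical events that meet the footnote's terms, two current passages give opposite answers on whether the remaining doses may be given. That concerns up to 3 of 4 doses for an event after the first dose, falling to none after the fourth. For other related grade 3 events and all related grade 4 events the texts agree. The mismatch between Table 5's causality labels and the Section 9.2.1 scale is a lesser defect in the same rule.

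This conclusion rests on reading both passages as current text of equal standing, since the protocol states no order of precedence. It does not depend on any assumed event rate. Because it concerns an individual stopping rule in a first-in-human safety study, it is more than clerical and should be corrected.

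**What to change.** Reconcile the synopsis entry with Table 5 and its # footnote so that all three state one rule. Align Table 5's causality categories with the Section 9.2.1 scale, so that Unlikely has a stated place and Unknown is either defined or removed. Which rule applies, and where Unlikely belongs, are clinical decisions for the sponsor's clinical team; none is proposed here. The cost is a text correction in a protocol amendment, with no change to sample size, visit schedule or planned analyses.
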